#### Secondary outcomes

Secondary outcomes include change in mental health difficulties, treatment readiness, and service utilization from pre (baseline) to mid (after 2 weeks) and post (after 4 weeks). Mental health difficulties will be assessed with the Depression, Anxiety, and Stress Scale 21 (DASS-21) [37] and the Strengths and Difficulties Questionnaire (SDQ) [38, 39]. Treatment readiness will be assessed with the treatment readiness subscale of the Motivation for Youth’s Treatment Scale (MYTS) [40]. Service utilization will be assessed with a researcher-generated scale.

The DASS-21 is 21 items and asks respondents how much specific statements applied to them over the previous week on a 4-point scale ranging from 0 (*never*) to 3 (*almost always*). We will examine change in overall psychological distress via the total DASS-21 score and change in specific domains via the three 7-item DASS-21 subscales. Total scores range from 0 to 63 with higher scores indicating greater psychological distress. Subscales are as follows: depressive symptoms (e.g., “I couldn’t seem to experience any positive feeling at all”), anxious symptoms (e.g., “I was aware of dryness of my mouth”), and stress (e.g., “I found it hard to wind down”). Subscale scores range from 0 to 21 with higher scores indicating greater symptoms/stress.

The SDQ is 25 items and asks respondents how true an item is for them over the last 6 months on a 3-point scale ranging from 0 (*not true*) to 2 (*certainly true*). We will examine change in overall difficulties via the total SDQ score (with exception of prosocial items) and change in specific strengths and difficulties via the SDQ subscales. Total scores range from 0 to 40 with higher scores indicating more difficulties. Subscales are as follows: emotional problems (e.g., “I worry a lot”), conduct problems (e.g., “I get very angry and often lose my temper”), hyperactivity (e.g., “I am constantly fidgeting or squirming”), peer problems (e.g., “I would rather be alone than with people of my age”), and prosocial behavior (e.g., “I try to be nice to other people. I care about their feelings”). Subscale scores range from 0 to 10 with higher scores indicating more difficulties (except the prosocial subscale where lower scores indicate more difficulties).

The treatment readiness subscale of MYTS is 4 items (e.g., “I want help finding solutions for my current problems”) and asks respondents how strongly they agree or disagree with each statement on a 5-point scale ranging from 1 (*strongly disagree*) to 5 (*strongly agree*). The subscale score ranges from 4 to 20 with higher scores indicating greater readiness.

The service utilization scale is 5 items and asks respondents about the frequency of healthcare services utilization (i.e., number of visits for/with: walk in clinic, family doctor or nurse practitioner, emergency department, mental health counselor, mental health hotline/phone support) over the prior 2 weeks. Items will be analyzed individually and as a total score across service types.

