### Trial design {8}

A pragmatic, parallel arm randomized controlled superiority trial will be used. Participants will be randomly allocated in a 1:1 ratio to the control (usual practice; UP) or intervention (UP + JoyPop) condition. Stratified block randomization will be used to randomly assign participants to each condition. All participants will be monitored through existing waitlist management practices, which involve regular phone calls to check in and assess functioning. Participants in the intervention condition will receive access to the JoyPop app for 4 weeks and be asked to use it at least twice daily. All participants will be asked to complete primary (emotion regulation) and secondary (mental health symptoms, treatment readiness, service utilization) outcome measures at pre (baseline), mid (after 2 weeks), and post (after 4 weeks) timepoints.

The Standard Protocol Items: Recommendations for Intervention Trials (SPIRIT) guidelines are being followed. The trial was registered with ClinicalTrials.gov (NCT05898516). All procedures have been reviewed and approved by the Research Ethics Board at the Thunder Bay Regional Health Sciences Centre (acting as the Board of Record for Lakehead University clinical research projects) and the Research Advisory Committee at our partner organization, Dilico Anishinabek Family Care (“Dilico”).

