### Outcomes {12}

#### Primary outcomes

The primary outcome is change in emotion regulation skills from pre (baseline) to mid (after 2 weeks) and post (after 4 weeks). Emotion regulation will be assessed with the Difficulties in Emotion Regulation Scale—Short Form (DERS-SF) [35, 36]. The DERS-SF is 18 items and asks respondent how often specific statements applied to them over the previous 2 weeks on a 5-point scale ranging from 1 (*almost never*) to 5 (*almost always*). We will examine change in overall emotion regulation via the total DERS-SF score and change in specific domains via the DERS-SF subscales. Total scores range from 18 to 90 with higher scores indicating greater difficulties in emotion regulation. Subscales are as follows: strategies (e.g., “When I was upset, I believed there was nothing I could have done to make myself feel better”), non-acceptance (e.g., “When I was upset, I became irritated with myself for feeling that way”), impulse (e.g., “When I was upset, I became out of control”), goals (e.g., “When I was upset, I had difficulty getting work done”), awareness (e.g., “I paid attention to how I feel”), and clarity (e.g., “I had no idea how I was feeling”). Total subscale scores range from 3 to 15 with higher scores indicating greater difficulty.

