### Implementation {16c}

After participants complete the measures at pre (baseline), the research assistant will obtain and open the next sequenced envelope to determine the allocation and inform the participant.

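### The SDQ's 6-month recall window is 85 to 92% pre-randomisation at the 2- and 4-week visits, so SDQ change is biased toward no effect by an unknown amount

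*Protocol article*

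**What the plan says.** Under Secondary outcomes, the protocol article lists "change in mental health difficulties, treatment readiness, and service utilization from pre (baseline) to mid (after 2 weeks) and post (after 4 weeks"). Two instruments carry the mental health part: the DASS-21 and the SDQ. On the SDQ it says "The SDQ is 25 items and asks respondents how true an item is for them over the last 6 months", and "We will examine change in overall difficulties via the total SDQ score (with exception of prosocial items"), together with change on five subscales (emotional, conduct, hyperactivity, peer, prosocial). That makes six SDQ change comparisons.

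Two other sections fix the timing. Implementation {16c} states: "After participants complete the measures at pre (baseline), the research assistant will obtain and open the next sequenced envelope". Trial design {8} states: "Participants in the intervention condition will receive access to the JoyPop app for 4 weeks". Time since baseline is therefore essentially time since randomisation.

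The other outcomes with a stated recall period have short windows. The DERS-SF "asks respondent how often specific statements applied to them over the previous 2 weeks", the DASS-21 "asks respondents how much specific statements applied to them over the previous week", and the service utilization scale covers the prior 2 weeks. No shorter SDQ window is given for the follow-up visits, and the article does not discuss the mismatch.

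**The concern.** A change score can register an intervention only through the part of the recall period in which the intervention could act. With a 6-month window and visits at 2 and 4 weeks, the baseline and follow-up forms ask largely about the same past weeks. The app, started after baseline, cannot alter those weeks. To the extent that respondents follow the instruction and draw on them, both arms' answers are anchored to shared pre-randomisation time and the difference between arms shrinks.

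The first secondary objective is at stake: whether the app changes mental health difficulties during the wait. The SDQ is one of only two instruments for it. It is also the one that covers conduct, hyperactivity, peer problems and prosocial behaviour, which the DASS-21 subscales (depression, anxiety, stress) do not. A flat SDQ result could be taken as evidence of no effect in those domains when the form asked mainly about the time before the app.

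**Working it through.** **Inputs from the protocol article**
- SDQ recall: 6 months, taken as 26 weeks (Secondary outcomes).
- Follow-up: 2 and 4 weeks after baseline, with allocation directly after baseline (Secondary outcomes; Implementation {16c}).
- Sample size basis: f = 0.2, alpha 0.05, power 0.95, 66 evaluable, 110 enrolled (Sample size {14}). This is for the primary outcome; no power is stated for the SDQ.

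**Step 1. The plan's own figure.** For the group-by-time interaction in a 2 × 3 mixed design, the noncentrality is λ = f² × N × 3 / (1 − ρ), with df 2 and 2(N − 2). The article gives no ρ; I assume 0.5. At N = 66, λ = 0.04 × 66 × 3 / 0.5 = 15.84 and power is 0.950; at N = 64 it is 0.944. Then 66 / 0.6 = 110. The stated figures reproduce.

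**Step 2. Share of the window before randomisation**, 1 − w/26:
- week 2: 24/26 = 92.3%
- week 4: 22/26 = 84.6%

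Counting 6 months as 24 weeks gives 91.7% and 83.3%, so the convention does not matter.

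**Step 3. Share of the effect retained.** The document does not say how respondents weight the window, so this is a range over assumptions. In every row the full effect is assumed to be present from the first day, which favours the SDQ.
- Even weighting: w/26.
- Recency weighting with half-life h weeks: (1 − 2^(−w/h)) / (1 − 2^(−26/h)).

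| Weighting (assumed) | Week 2 | Week 4 |
|---|---|---|
| Even | 7.7% | 15.4% |
| Half-life 8 weeks | 18% | 33% |
| Half-life 4 weeks | 30% | 51% |
| Half-life 2 weeks | 50% | 75% |

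**Step 4. What that could mean for power (illustration only).** Suppose the true SDQ effect were as large as the f = 0.2 planned for the primary outcome, and scale the whole effect by the week-4 share. This is generous, since week 2 retains less. Using the Step 1 formula with N = 66 and ρ = 0.5:

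| Share retained | f | Power |
|---|---|---|
| 100% | 0.200 | 95% |
| 75% | 0.150 | 76% |
| 51% | 0.101 | 41% |
| 33% | 0.065 | 19% |
| 15.4% | 0.031 | 8% |

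The loss runs from moderate to almost complete, depending on an unknown weighting.

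**Step 5. The other instruments.** The DASS-21 (1 week), DERS-SF (2 weeks) and service scale (2 weeks) have windows that fall wholly after randomisation at both follow-ups. The dilution is specific to the SDQ.

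**The case against.** The strongest reply is that share of window is not share of effect. The SDQ uses a how-true rating with present-tense items, not a count of events over time, and young people may answer mainly from how they are now. That stands. A reader might infer from the 85 to 92% overlap that any SDQ effect is nearly erased, or that the instrument cannot show one. The document does not support that: it holds only under even weighting, and the recency rows in the table keep up to three quarters of the effect at week 4.

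The power illustration is also limited. The plan states no SDQ effect size, ρ is assumed, and 66 is the planned number of completers, whereas the analysis is to include all randomised participants using full information maximum likelihood. The table therefore shows direction and range, not a forecast. Likelihood-based handling of missing data does nothing for recall dilution, however.

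The reach is narrow. The bias runs toward zero and creates no false benefit. The DASS-21 serves the same objective, and the article nowhere says that a null SDQ result would be read as no effect.

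Finally, the article describes the SDQ once and does not reproduce the follow-up form. That 6 months applies at every visit is the natural reading, but it is an inference.

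What survives is that, with the form as described, any use of the pre-randomisation weeks attenuates the SDQ effect, and the plan makes no allowance for it.

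**Conclusion.** The point holds as a measurement limitation of one secondary instrument. As described, 92% and 85% of the SDQ recall windows at weeks 2 and 4 precede randomisation, and the SDQ treatment effect is biased toward zero. The size of the bias is unknown. Retention is about 8% and 15% under even weighting, and about 18 to 50% (week 2) and 33 to 75% (week 4) for assumed half-lives of 8 down to 2 weeks.

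This rests on three things: the 6-month wording applying at follow-up, respondents using at least some of the earlier period as instructed, and an effect that begins no earlier than allocation. The primary DERS-SF analysis, the DASS-21 and the sample size of 66 (110 enrolled) are not touched. What changes is what the trial may conclude from a flat SDQ result under the first secondary objective.

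**What to change.** First, check the forms printed for weeks 2 and 4. If they already use a shorter window, correct the SDQ description under Secondary outcomes and state the window used at each visit.

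If they use 6 months, amend the plan for the running trial as follows:
- Name the DASS-21 (1-week recall) as the measure on which short-term inference about mental health difficulties rests.
- Keep collecting and reporting SDQ total and subscale change, labelled supportive or exploratory, with the recall limitation stated.
- State that a null SDQ change will not be interpreted as absence of effect.

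Do not shorten the recall wording for only some visits or participants. The trial began in May 2023. Changing only the follow-up forms would set a short window against a 6-month baseline in the linear and quadratic time contrasts, and a mid-trial switch would give participants different instruments. Dropping the SDQ as an outcome is not needed either, and would remove a published secondary outcome.

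The cost is one documented amendment, with the registry entry updated to match and no change to forms or visits. Six SDQ comparisons are downgraded, and conduct, hyperactivity, peer problems and prosocial behaviour lose confirmatory weight, since the DASS-21 does not cover them.

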#### Exploratory measures

Exploratory outcomes include an evaluation of app quality at post (after 4 weeks) among the intervention group. App quality will be assessed with the User Version of the Mobile Application Rating Scale (uMARS) [41]. The uMARS is 27 items and asks respondents to rate the quality of the app across each item on a 5-point scale ranging from 1 (*inadequate*) to 5 (*excellent*). We will evaluate app quality overall via the total uMARS score and app quality within specific domains via the uMARS subscales. Total scores range from 1 to 5 with higher scores indicating greater quality. Subscales are as follows: engagement (e.g., “Is the app fun/entertaining to use? Does it have components that make it more fun than other similar apps?”), functionality (e.g., “How accurately/fast do the app features (functions) and components (buttons/menus) work?”), esthetics (e.g., “How high is the quality/resolution of graphics used for buttons, icons, menus and content?”), information (e.g., “Is app content correct, well written, and relevant to the goal/topic of the app?”), subjective (e.g., “Would you recommend this app to people who might benefit from it?”), and perceived impact (e.g., “This app has increased my awareness of the importance of addressing the health behavior”). Subscale scores range from 1 to 5 with higher scores indicating more difficulties.

#### Descriptive measures

Descriptive information will be obtained through a demographic questionnaire at pre (baseline). Items will assess age, ethnicity, family composition, highest level of education, gender, sex at birth, sexual orientation, and living situation. Symptom presentation will be assessed with the DSM-5 Self-Rated Level 1 Cross-Cutting Symptoms Measures [42] at pre (baseline). The original measure is 25 items; however, we removed one item related to previous suicide attempts as per our community partner’s request. Respondents are asked to rate how much (or how often) they have been bothered by the specific symptoms during the past 2 weeks. Nineteen of the items are rated on a 5-point scale (*0* = *none or not at all; 1* = *slight or rare, less than a day or two; 2* = *mild or several days; 3* = *moderate or more than half the days; and 4* = *severe or nearly every day*). The suicidal ideation and substance abuse items are rated using a “Yes or No” scale. Scores will be summarized across the 12 psychiatric domains (i.e., depression, anger, irritability, mania, anxiety, somatic symptoms, inattention, suicidal ideation, psychosis, sleep disturbance, repetitive thoughts and behaviors, and substance use) and used to characterize the sample.

### Participant timeline {13}

### Sample size {14}

Our past research suggests a medium effect for the primary outcome [43]. We estimated conservatively in calculating sample size, using *f* = 0.2 (small to medium effect), alpha = 0.05, and power = 0.95 for a 2 (between subjects; treatment condition) by 3 (within subjects; time) mixed design, which approximates the statistical power needed for the planned linear mixed model under the assumption of compound symmetry (i.e., homogeneity of variance and covariance) [44]. Results suggested a sample size of 66 would achieve necessary power. Given our pilot data [34], we estimate 60% retention throughout the study (40% attrition), meaning we will need an initial sample size of 110.

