## Assignment of interventions: allocation

### Sequence generation {16a}

Participants will be randomly allocated in a 1:1 ratio to the control (UP) or intervention (UP + JoyPop) condition. Stratified block randomization will be used to randomly assign participants to each condition. Randomization will be conducted by a researcher not affiliated with the trial using a computer-generated sequencing tool [45].

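### The sample size of 66 is computed correctly, but f = 0.2 in that calculation is a between-arm difference of about 0.85 to 0.98 SD, not a conservative small-to-medium effect

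*Protocol article*

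**What the plan says.** Sample size {14} opens with the basis for the effect: "Our past research suggests a medium effect for the primary outcome". It then says "We estimated conservatively in calculating sample size", with f set at "0.2 (small to medium effect), alpha = 0.05, and power = 0.95". The design is a "2 (between subjects; treatment condition) by 3 (within subjects; time) mixed design", used as an approximation to the planned linear mixed model "under the assumption of compound symmetry (i.e., homogeneity of variance and covariance". The result is given as "Results suggested a sample size of 66 would achieve necessary power", and the allowance for loss follows: "we estimate 60% retention throughout the study (40% attrition), meaning we will need an initial sample size of 110". Sequence generation {16a} gives 1:1 allocation, so 66 is 33 per arm.

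The section does not give the correlation between visits, does not say which effect in the mixed design is tested, and does not translate f into a difference between arms in DERS-SF points or SD units. Statistical methods {20a} plans linear and quadratic contrasts over time and will report effects as a form of Cohen's d (the Feingold adaptation). Primary outcomes {12} defines the outcome as change from baseline to both the 2-week and the 4-week visit.

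**The concern.** A reader takes the paragraph to mean that the trial has 95% power for a modest benefit, and that this was a cautious choice because a larger effect was expected. That reading carries the usual size labels for f (0.10 small, 0.25 medium) from a comparison of independent group means, where two groups give d = 2f and f = 0.2 would be 0.4 SD. In a condition-by-time interaction, f measures something else: the spread of the interaction means across six cells. Part of that spread is used up by the baseline visit, where randomisation makes the expected difference zero. The same f then corresponds to a much larger difference at week 4.

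The stake is interpretation. With 95% power on record for a small-to-medium effect, a non-significant result invites the conclusion that the app has no medium-sized benefit, when the trial could well have missed one.

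**Working it through.** **Inputs.** From Sample size {14}: f = 0.2, alpha = 0.05, power = 0.95, k = 2 groups, m = 3 visits, compound symmetry, 40% attrition. From Sequence generation {16a}: 1:1 allocation. Assumed: the correlation rho.

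**Step 1. Reproduce 66.** For the within-between interaction, λ = f²·N·m/(1 − rho), with df1 = (k − 1)(m − 1) = 2 and df2 = (N − k)(m − 1).
- At rho = 0.5 and N = 66: λ = 0.04 × 66 × 3 / 0.5 = 15.84, df 2 and 128, power 0.9504. N = 64 gives 0.944, so 66 is the smallest even N.
- Other correlations give other answers: N = 92 at rho 0.3, 80 at 0.4, 54 at 0.6, 42 at 0.7.
- A between-groups main effect would need 220, and f derived from partial eta-squared would need 198.
- 66 / 0.60 = 110.

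The source of 66 is therefore the interaction formula with rho = 0.5.

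**Step 2. Convert f to a difference between arms.** Let δ₁, δ₂, δ₃ be the between-arm differences at the three visits in SD units, with δ₁ = 0. The interaction effects are ±(δⱼ − mean δ)/2, so f = SD(δ₁, δ₂, δ₃)/2, using the population SD.
- Linear growth (0, d/2, d): variance d²/6, so f = d/√24 = 0.2041d, and f = 0.2 gives d = 0.98.
- Reached at week 2 and kept (0, d, d): variance 2d²/9, so f = d/√18 = 0.2357d, and f = 0.2 gives d = 0.85. Benefit appearing only at week 4 (0, 0, d) gives the same.

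Rho does not enter this conversion.

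**Step 3. Power for 0.4 and 0.5 SD, 2-df interaction test** (lower figure linear profile, upper figure plateau):

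| N complete | rho | d = 0.4 | d = 0.5 |
|---|---|---|---|
| 66 | 0.3 | 21–27% | 31–40% |
| 66 | 0.5 | 28–36% | 42–54% |
| 66 | 0.7 | 44–56% | 64–77% |
| 66 | 0.8 | 62–75% | 82–92% |
| 110 | 0.5 | 45–57% | 64–77% |

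Simulation of the 2 × 3 F test at 33 per arm and rho = 0.5 agrees: 95% for (0, 0.49, 0.98) and (0, 0.85, 0.85); 28% and 36% at d = 0.4; 42% and 54% at d = 0.5. (The last figure is 53.5% by the formula and 53.8% by simulation.)

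**Step 4. The planned linear contrast.** With visits at 0, 2 and 4 weeks, the linear contrast is week 4 minus baseline. The SD of change is √(2(1 − rho)) = 1 at rho = 0.5, and the standard error with 33 per arm is √(2/33) = 0.246. The noncentrality is 0.4/0.246 = 1.62 or 0.5/0.246 = 2.03. On 64 df, power is 36% at 0.4 SD and 52% at 0.5 SD. The detectable difference is 0.70 SD at 80% power and 0.90 SD at 95%.

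**Step 5. For scale.** At rho = 0.5, 95% power on the 2-df test would need about 292 to 388 evaluable participants at 0.4 SD, or 188 to 250 at 0.5 SD.

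**The case against.** The strongest reply is that nothing is miscalculated. At the f the protocol states, 95% is correct, and on the f scale 0.2 does lie below the conventional medium of 0.25. The protocol never says that f = 0.2 means 0.4 or 0.5 SD. The first part stands: a reader might infer that the 95% or the 66 is an arithmetic error, and neither is. The second part does not rescue the label, because it describes group means in a between-subjects comparison, whereas the number 66 comes from an interaction formula.

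A reader might also infer that f = 0.2 is demonstrably larger than what the team's past research found. The documents do not support that. The cited study is not shown. If it reported f or partial eta-squared from a similar repeated-measures design, f = 0.2 could be below it; if it reported a standardised mean difference of about 0.5, f = 0.2 is well above it.

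The low power figures can be challenged too. They rest on an inferred rho and on a 2-df test, while the protocol plans polynomial contrasts and, under {20c}, keeps all randomised participants through likelihood estimation. These points stand as reasons to give a range. They do not restore 95% at the rho = 0.5 that yields 66: the linear contrast gives 36% and 52%; constraining baseline means to be equal gives about 46% and 64% for the week-4 difference; and 110 complete participants, an upper bound, give at most 57% and 77% on the 2-df test. Reaching 95% takes two favourable departures together. For example, rho = 0.8 with all 110 complete and a linear 0.5 SD gives λ = (0.25/24) × 110 × 3 / 0.2 = 17.2 and power of about 97%. Neither assumption is the protocol's own: 66 implies rho = 0.5, and 40% attrition is expected.

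**Conclusion.** The point holds as a misdescribed effect size. The calculation was made for a week-4 difference of about 0.85 to 0.98 SD, which is large on the standardised-difference scale the trial will report. It does not give 95% power for a small-to-medium effect if that is read as 0.4 to 0.5 SD.

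The conversion assumes no expected difference at baseline and a linear or plateau (or late) profile of benefit; it does not depend on rho. It also takes the Feingold-type d as the difference in change over the raw SD, since the article does not give the formula. The power figures do depend on rho, on the test and on how many participants contribute data.

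It would go too far to say flatly that the trial's power is 30 to 50%. That is roughly the 2-df result with 66 completers at rho = 0.5, not a property of the trial. It would also go too far to treat week 4 as the sole primary contrast, because the outcome definition names both follow-up visits.

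**What to change.** Keep 110 randomised and rewrite the paragraph:

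- Delete the claim that the estimate is conservative and the size label attached to f = 0.2.
- State that the tested effect is the condition-by-time interaction, and state the correlation used. The authors should confirm it; 66 implies 0.5.
- State that f = 0.2 corresponds to a between-arm difference in DERS-SF change of about 0.98 SD at week 4 under linear growth, or 0.85 SD if reached at week 2 and kept. Add DERS-SF points if an SD is available.
- Report power for 0.4 to 0.5 SD as a range over plausible correlations, for the interaction test and for the planned linear contrast. For the latter, the detectable difference with 66 completers and rho = 0.5 is about 0.70 SD at 80% power and 0.90 SD at 95%.
- State that a null result would not exclude a medium effect.

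The cost is one rewritten paragraph and a less favourable stated power. Design, analysis and recruitment target do not change.
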